### Follow- up evaluation

Follow-up is performed at 6 and 12 months at the outpatient clinic of the treating centers. Participants are contacted by telephone a couple of days prior to prevent drop out. At each evaluation appointment, the participants fill out the ATRS on a tablet.

All participants perform a warm up before testing: they ride a stationary bike for 5 min with minimal force and perform 3 × 10 single heel rises on both legs.

Firstly, the investigator will conduct ATRA followed by the heel-rise work test and registration of any complications or adverse effects. For this first part of the follow-up evaluation the participants will have tape placed on the back of the lower calf, so any surgical scare is covered in order to blind the investigator of the initial operative or non-operative treatment. Secondly, the investigator will conduct the CALM of both the total and the free part of the Achilles tendon, which is not possible to perform blinded.

### Registration and availability of data

All data are registered digitally in a web-based database (hosted by Procordo, Copenhagen, Denmark) especially designed for the trial. The registration forms are available from the first author upon request. The patients are given a patient identifier. All the results will be published at group level only and individual patients will not be able to be identified. At the completion of the study all identifiable data will be destroyed.

The project has been reported to the Danish Data Protection Agency, The Capital Region of Denmark, for all participating hospitals in the application (identifier AHH-2018-009, I-Suite no. 6356).

Data handling will be conducted in accordance with § 27 of the Danish Public Administration Act of patient confidentiality.

The patients will be informed, both verbally and in writing, that data are stored and analyzed in a computer, that the patient’s anonymity is preserved, and that the data protection legislation will be adhered to.

There will be free access to the final anonymized trial dataset. Due to the limited size of the study and the safety of the treatments, a data monitoring committee is not considered necessary.

#### Sample size

A difference in limb symmetry index for heel-rise work of 10% is considered clinically relevant. Based on the study by Silbernagel et al. [18], a standard deviation of 20 can be expected. The level of significance is set to *p* < 0.05 (C_2α_ = 1.96) and power is set at 90% (C_β_ = 1.281). The number of patients to be included in each treatment group is then calculated by: *N* = 2 × (C_2α_ + C_β_)^2^ × (SD)^2^/Δ^2^. Eighty-four patients have to be included in each group. Due to the risk of patient dropout, 100 will be included in each group. In total, 300 patients will be included. The incidence rate of patients with an acute Achilles tendon rupture at each hospital have been calculated and, based on previous experience, we expect being able to include 50% of patients passing through the departments.

#### Analysis of endpoints

Demographic parameters will be presented for each treatment group with mean and standard deviation (SD) or median and interquartile range (IQR) for continuous parameters and frequencies and percentages for categorical parameters.

Difference in Heel-rise work test will be tested by *t*-test or, if data can’t be assumed to be normally distributed, Wilcoxon sum rank test. Test will be made for the comparison individual vs operative treatment and individual vs non-operative treatment. To account for possible confounders, a linear regression will also be fitted for each comparison. Confounders include, but are not limited to, sex, age, BMI, and ATRS pre-injury; the confounding effect of these variables will be evaluated in the model by including and removing the variable and evaluating the change between the treatment group estimates.

Differences in severe complications (yes/no) between individual and operative treatment will be tested by chi-square test or, if the amount of expected observations for a single combination is less than 5, Fishers exact test. Additionally, the test will be adjusted for possible confounders in a logistic regression model; possible confounders and evaluation of these will be done as described in the Heel-rise work test models. Similar tests and models are made for the comparison of individual and non-operative treatments. Differences between individual and operative treatment and individual and non-operative treatment for all other secondary outcomes will be tested by *t*-test or Wilcoxon sum rank test.

All analysis will be done as intention-to-treat (ITT), that is, each patient is analyzed according to the treatment group they are randomized to. The results will therefore be interpreted as the effect of offering the patient the specific treatment options, regardless of if they complete them or not. Missing data will be imputed by multiple imputation, with imputation models based on available variables believed to be predictive of the missing measures. Additionally, the analysis for the primary outcome will be conducted as per protocol analysis, with per protocol defined as patients complying with the assigned protocol.

No interim analyses will be done.

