It is likely that some patients with primary Achilles tendon rupture need surgery and some are better off with non-operative treatment. This could be due to the individual morphology of the ruptured tendon and the potential to heal with good strength and a functionally acceptable length [13]. The identification and selection of patients for operative treatment has not yet been well investigated [14, 15]. The clinical criteria for recommending operative treatment differ and have not been derived from evidence. Some clinicians would recommend operative treatment for young patients with high functional demands and others would say that this should be avoided if the patient has a poor prognosis of healing based on comorbidities. These aspects clearly need to be taken into consideration but cannot stand alone. A quantitative and evidence-based measure or method is needed to guide the clinician for optimal treatment. Amlang et al. [14] have developed an ultrasonographic classification of Achilles tendon rupture but have not evaluated the length of the tendon or functional outcome after healing, and the method demands an experienced examiner. Barfod et al. have developed and validated the ultrasound-based Copenhagen Achilles Length Measure (CALM), which can be conducted in the emergency department as part of the primary diagnosis [16, 17]. Barfod et al. have also investigated the correlation of Amlang’s classification and CALM in the acute setting to functional outcome scores after 1 year in non-operative-treated acute Achilles tendon rupture. CALM was able to predict the final length of the tendon at one-year follow-up (manuscript in press). CALM is the base of the newly developed Copenhagen Achilles Rupture Treatment Algorithm (CARTA) together with examination of tendon overlap inspired by Amlang’s classification system [14], which may be used as a predictive tool for identifying patients at risk of critical elongation of the tendon after healing and poor functional outcome. A manuscript on CARTA has been submitted to a scientific journal.

Based on CARTA we propose an evidence-based, individualized algorithm for treatment of acute Achilles tendon rupture. The objective of this trial is to investigate if this algorithm is superior to both operative and non-operative treatment.

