### Secondary outcome measures

The secondary outcome measures are listed below (the timing of the assessments is shown in Fig. 1).
Copenhagen Achilles Length Measure (CALM) [19] is an ultrasonographic measurement of tendon elongation. It comprises two measurements (Fig. 2): the total length of the Achilles tendon (free tendon and fascia) and the free length of the Achilles tendon. The measurements are preformed the same way; they have the same distal landmark but the proximal landmark differs. CALM has shown good reliability and is recommended over other measurements of elongation [17, 20, 21]. The measure is performed as described by Barfod et al. but with the feet of the patient (laying in the prone position) hanging free of the table instead of with 10° degrees of plantar flexion in the ankle joints as originally described [16, 21]. Landmarks are identified and marked on the skin. The distal landmark is the posterior and most superior part of the calcaneus in the midline, which on sagittal ultrasound examination is identified as the point where the cortical bone and its underlying shadow end. The proximal landmark for the total length of the Achilles tendon is the distal tip of the medial gastrocnemius head, which on sagittal ultrasound examination is recognized as the point where the most distal muscular fibers are inserted into the deep crural fascia. The proximal landmark for the free length of the Achilles tendon is the distal tip of the soleus muscle, which is defined at the point where the most distal muscular fibers insert into the Achilles tendon. The distance between these two points on the un-injured leg defines the total length of the Achilles tendon and the free length of the Achilles tendon, respectively. The differences between the non-injured and the injured leg are defined as tendon elongation. At inclusion only the total Achilles tendon length is measured for both legs. The examination of both the total and the free part of the tendon of both the injured and un-injured leg is performed at 6- and 12-month follow-up. The position of the feet also differs between inclusion and follow-up. During inclusion, the originally described position of the feet is used (10° of plantar flexion in the ankle joints) but during the 6- and 12-month follow-up, the feet hang free of the table.Heel-rise work test: The test is conducted as described for the primary endpoint and conducted as a secondary endpoint at 6 months.Achilles tendon resting angle (ATRA) [22]: ATRA is an indirect measurement of tendon elongation. The patient lies flat in the prone position on the examination bed. The knee is flexed at 90 degrees and the ankle sits in a relaxed position. The ATRA is determined as the angle between the longitudinal axis of corpus of the fibula and the longitudinal axis of corpus of the fifth metatarsus. ATRA is determined for both the injured and the uninjured leg. The difference between the healthy and the injured leg is evaluated. ATRA has shown excellent reliability [22, 23].Complications: Incidence rates of the commonly known complications and adverse events such as infection, re-rupture, permanent sural nerve dysfunction, deep venous thrombosis, adhesions, and pain at the scar are noted. Attention is also paid to unknown complications in relation to the treatments.Achilles tendon Total Rupture Score (ATRS) [24]: Patients fill out the ATRS questionnaire at inclusion and after 6 and 12 months in connection with the follow-up visits in the outpatient clinic. ATRS is a patient-reported outcome measure developed to assess symptoms and physical activity after treatment for acute Achilles tendon rupture. The Danish version was found to have good validity and be reliable to use for comparison on the group level [25].Tegner Activity Scale: A scale that aims to provide a standardized method of grading work and sporting activities. Tegner activity scale is a graduated list of activities of daily living, recreation, and competitive sports. The patient is asked to select the level of participation that best describes their level of activity at inclusion and at 6 and 12 months after rupture and before injury [26].Calf circumference: The patient sits on an examination bed with legs hanging down. The circumference of the calf is measured using a measuring tape (13 cm under apex patella).MRI: MRI of the calf is performed after 1 year for the first 60 patients included at Copenhagen University Hospital Amager-Hvidovre. MRI will be conducted to obtain a deeper understanding of changes to the different structures in the muscle–tendon complex during the first year after rupture. The MRI will be conducted at Copenhagen University Hospital Amager-Hvidovre in an Acanto 1.5 T scanner. Both lower legs will be scanned.Gait analysis: Gait analysis is performed after 6 and 12 months for the first 60 patients included at Copenhagen University Hospital Amager-Hvidovre. The gait analysis will be conducted at the Gait Laboratory, Copenhagen University Hospital Amager-Hvidovre. Twenty-two reflective markers are placed on the patient’s skin with tape on specific anatomical locations, as described by Speedtsberg et al. [27]. The participants are instructed to walk barefoot at a self-selected speed on a 10-m level walkway. The reflective markers are filmed by eight infrared cameras, whereby the joint angles during gait are measured. In combination with the ground reaction forces from two force plates embedded in the floor, the joint moments and powers will be calculated.

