### Randomization

Randomization is computer based following the random allocation rule to ensure balanced group sizes. Randomization is facilitated through a web-based database hosted by Procordo, Copenhagen, Denmark. The software will produce an allocation number for the patient to one of the groups: 1) intervention group, 2) control group A, or 3) control group B. Block randomization will be conducted with the participants individually randomized in a 1:1:1 order in blocks stratified by hospital to one of three parallel groups. The allocation key is stored by Procordo and only accessible by the project contact person at Procordo.

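### Randomisation is stratified by hospital, but the primary test ignores hospital and the planned regression neither names it nor would reliably keep it, so if hospital predicts outcome the test is conservative and precision is forgone

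*Protocol article*

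**What the plan says.** The protocol article, under Design and again under Randomization, has patients "individually randomized in a 1:1:1 order in blocks stratified by hospital to one of three parallel groups". There are four hospitals.

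Under Analysis of endpoints, the heel-rise work outcome is compared by a t-test, or by a Wilcoxon rank-sum test if normality cannot be assumed: "Test will be made for the comparison individual vs operative treatment and individual vs non-operative treatment". No hospital term or stratified version is mentioned. The same section adds a linear regression for each comparison. Its confounder list is expressly open; it names sex, age, BMI and pre-injury ATRS, but not hospital. Each candidate is assessed by putting it in, taking it out and seeing how the treatment estimate changes. The other secondary outcomes, apart from severe complications, get only a t-test or Wilcoxon test.

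Sample size rests on two inputs for the limb symmetry index: "A difference in limb symmetry index for heel-rise work of 10% is considered clinically relevant", and "a standard deviation of 20 can be expected". No reduction for covariates is taken.

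On baseline tendon length, Secondary outcome measures says: "At inclusion only the total Achilles tendon length is measured for both legs". The Background reports that "CALM was able to predict the final length of the tendon at one-year follow-up", in a cohort treated non-operatively.

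**The concern.** Stratified blocks make the arms nearly equal in hospital mix. Differences between hospitals therefore cancel out of the treatment contrast, but the two-sample standard error still counts them as noise. If hospital is related to outcome, the standard error is too large for the design actually used: the nominal 5% test rejects less often than 5% under the null, and the 95% interval covers more than 95%.

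The document gives some reason to expect hospital differences. Rehabilitation from week 13 is outside the trial's control and runs through each hospital's own municipalities (Discussion), and at one centre the physiotherapists are not blinded (Education and training).

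At stake is modest efficiency and correct calibration of the primary test. There is no risk of excess false positives.

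**Working it through.** **1. The plan's own figure.** Inputs from Sample size: difference 10, SD 20, C_2α = 1.96, C_β = 1.281.

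N = 2 × (1.96 + 1.281)² × 20² / 10² = 84.03, which reproduces 84 per group. Power of the unadjusted test at SD 20 is 90.0% with 84 per group and 94.2% with 100.

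**2. Effect of ignoring hospital.** Let R² be the share of outcome variance due to hospital. The document gives no value, so 0 to 10% is assumed. With perfect balance within hospital, the true standard error of the contrast is 20 × √(1 − R²) × √(2/84), while the t-test uses 20 × √(2/84) = 3.086. Under a normal approximation:

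- true alpha = 2 × [1 − Φ(1.96 / √(1 − R²))]
- excess interval width = 1/√(1 − R²) − 1
- half-width after adjustment = 1.96 × 3.086 × √(1 − R²)
- power of the unadjusted test under stratified allocation = Φ[(10/3.086 − 1.96) / √(1 − R²)]
- power with hospital in the model = Φ[10 / (3.086 × √(1 − R²)) − 1.96]

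| Assumed R² | True alpha | Excess width | Half-width, adjusted (unadjusted 6.05) | Power, unadjusted | Power, adjusted |
|---|---|---|---|---|---|
| 0 | 5.0% | 0% | 6.05 | 90.0% | 90.0% |
| 0.02 | 4.8% | 1.0% | 5.99 | 90.2% | 90.6% |
| 0.05 | 4.4% | 2.6% | 5.90 | 90.6% | 91.4% |
| 0.10 | 3.9% | 5.4% | 5.74 | 91.1% | 92.7% |

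In patients, 84.03 × (1 − R²) gives 82.4, 79.8 and 75.6 at R² of 0.02, 0.05 and 0.10. The unadjusted interval with 84 per group is thus about as wide as an adjusted one with 82, 80 or 76.

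**3. Simulation check.** This used 84 per group, four hospitals with assumed shares of 40/25/20/15%, exact balance within hospital and 6,000 runs per setting. The unadjusted test's type I error was 4.6% at R² = 0.05 and 4.0% at 0.10. At 0.02 it was 5.1%, which cannot be told apart from the calculated 4.8%, as the simulation error is √(0.05 × 0.95 / 6000) ≈ 0.3 points. With hospital in the model it stayed between 5.1% and 5.4%.

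**4. Would the planned regression pick hospital up?** If every hospital contributes the arms in equal proportion, the treatment difference is the same with or without hospital in the model. The change in estimate is then about zero, however strongly hospital predicts outcome; only the standard error changes. A rule that looks at the estimate cannot see this.

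**5. Inclusion elongation.** It is not a stratification factor, so leaving it out does not distort alpha or coverage and can cost only precision. The one strength figure given (sensitivity 77%, specificity 50%, in the CARTA section) concerns 1-year elongation of at least 10%. With prevalence p and test-positive share q = 0.77p + 0.50(1 − p), phi = 0.27 × √[p(1 − p) / (q(1 − q))]. For assumed p of 20 to 60%, phi² is about 0.05 to 0.08. No figure is given for heel-rise work.

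**The case against.** The strongest reply has four parts.

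- **An adjusted model is planned and its list is open.** Hospital could be added, and an analysis plan that is not shown may do so. This stands in part: it would be wrong to infer that no adjusted analysis exists. But the regression is additional to the stated primary test, and its selection rule works against a balanced factor.
- **Power is not lost against the target.** A reader might infer that the trial falls short of 90%. It does not: the SD of 20 is unadjusted, so the sample size already pays for the unadjusted test, and stratification moves its power slightly above 90%. This stands fully.
- **Hospital effects may be small.** The limb symmetry index uses each patient's own uninjured leg as reference, all centres use the same measuring system, standard treatment is described as the same, and testers are calibrated yearly. With up to 11 municipalities per hospital, much of the rehabilitation variation lies within hospitals, where a hospital term cannot absorb it. Unblinded assessment at one centre chiefly threatens a treatment-related bias, which a hospital main effect does not correct. This stands: R² may be close to zero.
- **Elongation is a weak candidate.** A reader might infer that omitting it also makes intervals too wide. The document does not support that: coverage stays correct, the reported prediction is of tendon length in non-operatively treated patients, and the Discussion concedes a sizeable individual measurement error. Table 1 puts randomisation and the CARTA decision in the same visit, and nothing says the scan comes first. This stands, so elongation can only be a conditional addition.

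**Conclusion.** The mismatch between a hospital-stratified allocation and a primary test that ignores hospital is real, and the planned regression is not a dependable remedy. The consequence is conservatism: for assumed hospital shares of 2 to 10%, true alpha is about 4.8% to 3.9%, the interval is 1.0% to 5.4% wider than needed, and adjusting would add about 0.3 to 1.6 points of power (90.2% to 90.6% at a 2% share; 91.1% to 92.7% at 10%). These figures assume exact balance within hospital, a total SD of 20 and 84 evaluable patients per group. With no hospital effect the cost is nil. The planned power is met either way and false positives are not inflated. The point is worth acting on because the change is cheap and makes the analysis match the design.

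**What to change.** Make the primary analysis a pre-specified linear model of the 12-month limb symmetry index on treatment group, with hospital as a fixed effect that stays in the model and is exempt from change-in-estimate selection. Report the two contrasts, CARTA against operative and CARTA against non-operative, from that model, and keep the unadjusted t-test or Wilcoxon test as supporting.

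Optionally, if it is confirmed that the inclusion scan is done before allocation in all three arms, name inclusion CALM elongation as a further pre-specified covariate, chiefly for the 12-month elongation outcome. Its effect is on precision only, and the size of the gain is unknown.

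The cost is analysis wording, settled before the data are unblinded. Hospital is already recorded as the stratification factor, and neither sample size nor trial conduct changes. The optional step also needs the check on scan timing.

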### Blinding

The investigators performing the functional follow-up evaluation are partly blinded to the intervention. Patients will wear tape over the Achilles region on the injured leg during the functional tests. The data from the blinded part of the examination are secured before the ultrasound examination is performed. The ultrasound examination is performed semi-blinded as it is impossible to cover the surgical scar during the scan. This examination is performed last. The investigator knows if the patient is treated operatively or not but does not know to which group the patient has been allocated. The data analysis will be conducted fully blinded. The patients are unblinded throughout the trial.

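### Covariates for the adjusted models are judged by how far they move the treatment estimate; a fixed set should replace this rule

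*Protocol article*

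**What the plan says.** All of this is in the protocol article, mostly under Analysis of endpoints.

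- The primary comparison is unadjusted: "Difference in Heel-rise work test will be tested by" a t-test, or a Wilcoxon test if normality fails, once for CARTA against operative and once for CARTA against non-operative treatment.
- A model is added: "To account for possible confounders, a linear regression will also be fitted for each comparison".
- The candidate list is open: "Confounders include, but are not limited to, sex, age, BMI, and ATRS pre-injury".
- Each candidate is judged "by including and removing the variable and evaluating the change between the treatment group estimates". The article gives no size of change that counts, no order of entry and no final model.
- Severe complications are first tested by chi-square or Fisher's exact test. A logistic model is then added, in which "possible confounders and evaluation of these will be done as described in the Heel-rise work test models".
- Under Randomization, patients are "individually randomized in a 1:1:1 order in blocks stratified by hospital to one of three parallel groups". Hospital is not among the named covariates.
- Under Blinding: "The data analysis will be conducted fully blinded".

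**The concern.** A change-in-estimate check is a tool for observational data, where a shift on adjustment can reveal systematic confounding. Here allocation is random, so a shift shows only that a covariate happened to differ between the groups. The useful reason to adjust is prognostic strength, which narrows the standard error whether or not the covariate is balanced. The rule asks a different question and has three consequences.

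- The set of covariates depends on the treatment estimate itself.
- A strong predictor that happens to be balanced looks unimportant and may be left out, so precision is lost.
- With an open list and no stated cut-off, several adjusted results are available and the plan does not say which one is reported. Because the check is run for each comparison, the two main contrasts may also end up with different covariates.

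The logistic model has a further problem. The odds ratio is non-collapsible: adjusting for a prognostic covariate changes it even when the groups are perfectly balanced. A change is then not evidence of confounding at all.

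**Working it through.** **1. The plan's own figure.** Sample size gives a difference of 10 ("A difference in limb symmetry index for heel-rise work of 10% is considered clinically relevant"), SD 20, and constants 1.96 and 1.281.

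N = 2 × (1.96 + 1.281)² × 20² / 10² = 2 × 10.504 × 4 = 84.03, which reproduces the stated 84. Power at 84 per group is 90.0%. The standard error of the unadjusted difference is 20 × √(2/84) = 3.09 points. This calculation rests on the unadjusted test, so the covariate rule does not touch it.

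**2. Which covariates a change rule keeps.** Assumptions that are not in the article: four independent, equally prognostic covariates, together explaining R² = 0.3 of the variance, and a cut-off of 10% of the estimate.

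- Effect of one covariate per SD: 20 × √(0.3/4) = 5.48 points.
- Chance imbalance between groups, in SD units: √(2/84) = 0.154.
- Typical shift from adjusting for one covariate: 5.48 × 0.154 = 0.845 points, whatever the true treatment effect.
- True difference 10: the shift must exceed about 1.0 point. P(|Z| > 1.0/0.845 = 1.18) = 0.24, so about 4 × 0.24 = 0.95 covariates are kept.
- True difference 0: the estimate has SD 3.09, so the cut-off is 0.309 × |Z|. For a ratio of two normals, P = 1 − (2/π) × arctan(0.309/0.845) = 0.78, so about 4 × 0.78 = 3.1 are kept.

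The hand calculation treats the shift and the estimate as independent. A simulation (84 per group, 4,000 runs) gives 1.02 and 3.05. The covariates are equally useful in both cases; only the treatment effect differs.

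**3. Power at a true difference of 10.** The table shows two separate simulations, divided by a slash. Ranges cover entering covariates one at a time and removing them from the full model.

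| Assumed R² | Fixed set | 10% change rule | Loss (points) |
|---|---|---|---|
| 0.1 | 91.8% / 91.5% | 90.5–90.9% / 90.5% | 0.9–1.3 / 1.0 |
| 0.2 | not run / 94.3% | not run / 92.7% | 1.6 |
| 0.3 | 96.8% / 96.9% | 94.7–95.2% / 94.9% | 1.6–2.1 / 2.0 |

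At R² = 0.3 the SD of the estimate is 2.61 with the fixed set and 2.78 to 2.81 under the rule. The theoretical value for the fixed set is 3.09 × √0.7 = 2.58.

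**4. Type I error.** Applied mechanically in both directions, the 10% rule gave 2.5% to 4.9% with four covariates (R² 0.1 to 0.5) and 3.4% to 3.9% with eight (R² 0.3). Other simulations at R² 0.1 to 0.3 gave 3.9% to 5.7%. Allowing for simulation error of about 0.35 to 0.4 points, there is no inflation.

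**5. What the open wording would allow.** If only covariates that move the estimate towards CARTA were kept, the null estimate would be biased by 0.6 to 1.7 points. False positives in CARTA's favour would rise from 2.5% to 5.1% (four covariates, R² 0.3) or 6.1% (eight covariates). Searching all 2⁴ = 16 models for the most favourable gives a type I error of about 8% to 14%. The article prescribes neither procedure.

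**The case against.** The strongest reply is that little depends on these models. The t-test or Wilcoxon test comes first, the regression is an addition, and the sample size rests on the unadjusted comparison. The same order holds for severe complications. This stands, and it limits the weight of the point. The article does not say which result prevails if the two disagree, so the adjusted models are not harmless.

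A reader might infer that the rule invalidates the adjusted p-values or raises the trial's false-positive rate to 8–14%. The document does not support that. The figure belongs to a search over all models, which is a worst-case misuse, and the mechanical rule shows no inflation. The p-value does ignore a selection step, but that is a weaker statement.

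A reader might also take the whole gain from 90% to 93–95% power (calculated for fixed adjustment at R² 0.1 to 0.2) as what the rule costs. That compares fixed adjustment with none; against the rule itself the loss is about 1 to 2 points.

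The blinded analysis limits choice in CARTA's favour. It does not remove the dependence on the size of the estimate or prevent a search for a small p-value.

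Finally, the article says that confounding will be evaluated and does not spell out that variables are kept or dropped. Selection is the natural reading, but it is a reading. A cut-off may stand in a separate analysis plan. That would settle the missing detail, but it would not make the stated criterion suitable for a randomised trial.

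**Conclusion.** The point holds for the additional linear and logistic models only. The criterion is one the article states, and it is the wrong one under randomisation: it makes the adjusted model depend on the treatment estimate (about 3 of 4 covariates kept at no effect, about 1 of 4 at a 10-point effect). It gives up about 1 to 2 points of power compared with a fixed set, and it leaves room for selective model choice. In the logistic model the criterion is also confused by non-collapsibility. That effect is small when events are rare, and the article gives no expected rate.

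The unadjusted tests and the 84 per group are unaffected, and inflated type I error is not shown for a mechanically applied rule. The sizes rest on assumed values: R² of 0.1 to 0.3, independent and equally prognostic covariates, and a 10% cut-off. This should be fixed, but it does not threaten the main unadjusted result.

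**What to change.** - Under Analysis of endpoints, delete the clause that leaves the confounder list open, and delete the include-and-remove step for both models.
- For each comparison, fit one pre-specified linear model of the 12-month limb symmetry index with treatment group, hospital (the stratification factor), sex, age, BMI and pre-injury ATRS. Keep all terms whatever they do to the estimate.
- Add CALM elongation at inclusion only if it is measured before allocation in all three arms. Secondary outcome measures describes an inclusion measurement on both legs. However, Table 1 puts inclusion and randomisation in the same visit without fixing when the measurement is made, and the CARTA section ties the ultrasound examination to the intervention group.
- For severe complications, report the unadjusted risk difference with its confidence interval, or adjust only for a small set fixed in advance.

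The cost is wording. The article already names sex, age, BMI and pre-injury ATRS as covariates, and hospital is known from the randomisation. Sample size and visits do not change. The edit should be made before the allocation is unblinded.
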